# Effects of exercise and horticultural intervention on the brain and mental health in older adults with depressive symptoms and memory problems: study protocol for a randomized controlled trial [UMIN000018547]

**DOI:** 10.1186/s13063-015-1032-3

**Published:** 2015-11-04

**Keywords:** Cognition, Depression, Exercise, Hippocampal volume, Horticulture

## Abstract

**Background:**

Depressive symptoms and memory problems are significant risk factors for dementia. Exercise can reduce depressive symptoms and improve cognitive function in older people. In addition, the benefits of horticultural activity on physical and mental well-being have been demonstrated in people with dementia. Although evidence of such non-pharmacological interventions is mounting, no studies have examined whether physical exercise and horticultural activity exert a positive impact on brain and mental health (e.g., depressive symptoms) in non-demented older adults at high risk of cognitive impairment and depression. Therefore, we propose a randomized controlled trial to assess the efficacy and efficiency of physical exercise and horticultural activity in improving brain and mental health in community-dwelling older adults with memory problems and depressive symptoms.

**Methods/Design:**

The 20-week randomized controlled trial will include 90 community-dwelling adults aged 65 years or older with memory problems and depressive symptoms. Participants will be randomized to one of three experiments: exercise, horticultural activity, or educational control group, using a 1:1:1 allocation ratio. The combined exercise program and horticultural activity program will consist of 20 weekly 90-minute sessions. Participants in the exercise group will practice aerobic exercise, muscle strength training, postural balance retraining, and dual-task training. The horticultural activity program will include crop-related activities, such as field cultivation, growing, and harvesting. Participants in the educational control group will attend two 90-minute educational classes during the 6-month trial period. Depressive symptoms and memory performance will be measured by the Geriatric Depression Scale-15, and the Logical Memory subtests of the Wechsler Memory Scale-Revised will be used to measure depressive symptoms and memory performance as primary outcomes, at baseline (prior to randomization), immediately following intervention (6 months from baseline), and 6 months after intervention. Hippocampal volume will be measured at baseline and immediately after intervention, using magnetic resonance imaging. Secondary outcomes will comprise cognitive function, including language, attention/executive performance, and processing speed; brain-derived neurotrophic-factor serum levels; and health-related quality of life.

**Discussion:**

This intervention study will determine the clinical importance and efficacy of physical exercise and horticultural activity as non-pharmacological interventions in community-dwelling older adults at high risk of poor brain and mental health.

**Trial registration:**

UMIN000018547; registered 7 August 2015.

## Background

Depressive symptoms constitute a significant risk factor for Alzheimer’s disease (AD) [1]. Epidemiological studies have reported an association between depressive symptoms and cognitive decline, and depressive symptoms have been shown to predict cognitive decline in old age [2–4]. Several factors affect cognitive functioning in old age, and older people with memory problems are considered to be at a higher risk of developing dementia, particularly AD, relative to those without memory problems [5, 6]. In addition, cognitive impairment is more common in older people with depression [7]. Therefore, older adults with combined memory decline and depressive symptoms may be at a higher risk of dementia, and they should be the focus of interventions designed to improve brain and mental health and address issues such as memory problems and depressive symptoms.

Exercise can improve cognitive function and reduce depressive symptoms in older people. Specifically, aerobic exercise has been shown to produce mild-to-moderate cognitive gains in healthy adults [8]. Cognitive improvement has also been observed following aerobic exercise in older adults with mild cognitive impairment (MCI) [9, 10]. However, evidence concerning the effects of aerobic exercise on memory in older adults with a higher risk of cognitive impairment is limited [11]. Some studies have shown memory improvement following exercise interventions involving physical and cognitive activities in participants with MCI [12, 13]. Interestingly, moderate-intensity physical exercise may increase hippocampal volume in cognitively healthy community-dwelling older adults [14] and those with MCI [15]. Hippocampal volume is the primary determinant of memory decline [16], and geriatric depression magnifies hippocampal atrophy and the risk of AD [17].

Exercise could also improve mood in older people. Antidepressant effects have been observed with exercise in people with mild depression [18]. A systematic review indicated that exercise was moderately more effective than a control intervention in reducing symptoms of depression, but analysis of methodologically robust trials showed a smaller effect in favor of exercise [19]. Results of another review were consistent with the suggestion that, for older people who present with clinically meaningful symptoms of depression, prescribing structured exercise with mixed elements of endurance and strength training tailored to individual ability is likely to reduce the severity of depression [20].

Another non-pharmacological intervention strategy for reducing depression is horticultural activity, which is expected to increase social and behavioral activation and mental well-being, and moderate levels of physical activity in a nature-based environment [21]. In addition, intervention studies, randomized controlled trials (RCTs), and pre–post design studies have been conducted to examine the effects of horticultural activity on physical and mental well-being in people with dementia, and the results showed reductions in levels of agitation [22]. However, the quantitative studies were of poor quality with respect to sample size and study design. In addition, there have been no well-designed intervention studies conducted to examine the effects of horticultural activity on brain and mental health (e.g., depressive symptoms, cognitive function, and brain volume) in non-demented adults with a higher risk of dementia.

We hypothesize that physical exercise and horticultural activity may exert a positive impact on brain (e.g., cognitive function and brain volume in the hippocampus) and mental health (e.g., depressive symptoms) in older adults with a higher risk of cognitive impairment and depression. However, this hypothesis has not been tested. Therefore, we propose a 20-week RCT involving community-dwelling adults aged 65 years or older with mild memory problems and depressive symptoms. Further, we aim to explore the relative importance of hippocampal volume changes with respect to improvements in cognitive function and mood. Given the immense health and financial burdens imposed by dementia and depression, the results of our proposed RCT could exert a significant impact on the health of Japanese seniors and the country’s long-term care system.

## Methods/Design

### Study design

The proposed study is a randomized single-blind controlled community-based trial with a parallel design and a 1:1:1 allocation ratio. The study design is shown in Fig. 1. We will recruit 90 community-dwelling adults aged 65 years or older with memory problems and depressive symptoms. Informed consent will be obtained from all participants prior to their inclusion in the study. The study protocol was approved by the Ethics Committee of the National Center for Geriatrics and Gerontology (#839).

**Fig. 1 Fig1:**
[figure not shown]
Overview of the flow of participants

### Setting

This study will be conducted in the Japanese community in Obu city, a suburb of Nagoya, Japan. Obu city has a population of 88,550, of whom 17,354 (19.6 %) are aged 65 or older (in April 2014). We have been conducting an observational study, including face-to-face interviews and measures of physical and cognitive function, in this community since 2011 [23]. Pre-intervention and post-intervention participant screening and data collection will be performed at the community center. Magnetic resonance imaging (MRI) scanning will be conducted at the Research Institute at the National Center for Geriatrics and Gerontology.

### Study population

The study population will include community-dwelling older adults with mild memory decline and depressive symptoms. Participants will be required to meet the following inclusion criteria: (1) independent adults aged 65 years or older living within the community; (2) memory problems (subjective memory complaints or objective mild memory decline indicated via an age-adjusted word list memory score at least 1.0 SD below the reference threshold); and (3) presence of depressive symptoms (Geriatric Depression Scale-15 [GDS-15] score of ≥5) [24]. Participants will be excluded if they meet the following exclusion criteria: (1) support or care certified by the Japanese public long-term care insurance system; (2) dementia diagnosis or Mini-Mental State Examination score of ≤18; (3) a history of major psychiatric illness (e.g., bipolar disorder) or other serious neurological or musculoskeletal diagnoses; (4) disability in basic activities of daily living; (5) incapable of undertaking cognitive performance tests; (6) physical exercise contraindication; and (7) use of walking aids in daily life. Participants will also be excluded if they cannot sign the informed consent form.

### Sample size

The required sample size for this study was calculated using predictions of 6-month changes in GDS-15 results. Based on the results of our previous work, conducted in the same town, we predict that a change of 1.5 GDS-15 points would indicate differences and assume that the SDs for the GSD-15 would be 2.5 in our sample. Assuming a non-consent and dropout rate of 20–30 %, 30 participants are required per group. The study design necessitates power of at least 80 % and an α level of <.05 to assess the effects of the interventions.

### Randomization

Participants will be randomly assigned (1:1:1) to an exercise intervention (EI), a horticultural intervention (HI), or an educational (control) group upon completion of baseline assessments. The randomization sequence will be computer generated [25, 26]. A researcher who is unaware of the aims of the study will perform the randomization procedure.

### Planned trial interventions

#### Exercise intervention group

The combined exercise program will involve 20 weekly 90-minute sessions involving physical and cognitive activities. Approximately 10–15 individuals will participate in each class at a fitness facility. Trained instructors will conduct the exercise sessions, which will involve aerobic exercise, muscle strength training, postural balance retraining, and dual-task training. Each session will begin with a 10-minute warm-up period and stretching exercises followed by 20 minutes of muscle strength exercise and postural balance retraining. The exercises will be conducted under multitask conditions that will include physical and cognitive tasks; we have called this combination training “cognicize.” For example, participants play word games while engaging in stepping exercises. The participants will also undertake daily home-based exercises and walking, which will require self-monitoring using a booklet and pedometer. To improve health behavior, physiotherapists will deliver lectures to inform the participants about cognitive health, exercise methods, the risks associated with dementia, effects of exercise on dementia, and ways in which to self-monitor regular physical activities.

#### Horticultural intervention group

The HI program will involve 20 weekly 90-minute sessions involving nature-based activities. The program will include crop-related activities such as cultivating a field, growing, and harvesting. Individuals in this group will engage in gardening activities including group planting (known as *Yoseue style bonsai*), which involves the combination of different plant varieties or shapes, and planting flowers in the public garden. The vegetable experts will lecture the participants with nutritional information and recipes for the field crops that will be grown in the program.

#### Educational control group

Participants in the educational control group will attend two 90-minute education classes during the 6-month trial period. The classes will include topics that experts consider less likely to influence study outcomes (e.g., effective remedies for crime or traffic accidents in older people).

### Outcomes

Outcomes will be measured at the community center by research assistants who are blinded to the randomization status. Participants will be required to take part in baseline data collection lasting approximately 2 hours. Subsequent data collection will occur immediately following the intervention (6 months after baseline) and 6 months after intervention for all outcomes. All outcome measures will be assessed by independent examiners who are unaware of group allocation.

#### Primary outcomes

Primary outcomes will include a reduction in depressive symptoms, based on changes in GDS-15 scores, and an improvement in memory performance, assessed via word list memory [27] and the Logical Memory subtests of the Wechsler Memory Scale-Revised (WMS-R) [28]. The GDS-15 consists of 15 items. A score of 5 or higher will be used to identify clinical depressive symptoms [29, 30].

The word list memory tasks will involve immediate recognition and delayed recall of a 10-word target list [27]. Participants are instructed to memorize 10 words, which are presented on a tablet personal computer. Each of the 10 target words is presented for 2 seconds. A total of 30 words, including 10 target and 20 distracter words, is then presented, and participants are asked to choose the 10 target words immediately (Word-List Memory Task I); this is repeated for three trials. The average number of correct answers is calculated to produce a score within a range of 0–10. In addition, participants are instructed to recall (and record in writing) the 10 target words after approximately 20 minutes (Word-List Memory Task II). The total number of target words recalled is then calculated.

In the WMS-R Logical Memory subtests, two short stories (A and B) are read aloud to the participant, who is instructed to recall the details of the stories immediately (Logical Memory Task I) and after 30 minutes (Logical Memory Task II) [28]. Total scores are calculated (i.e., sum of scores for stories A and B) for WMS-R Logical Memory Tasks I and II.

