### Statistical analyses

Statistical analyses will be conducted to assess the effects of interventions according to the intention-to-treat principle, which states that data for all individuals should be analyzed according to their group allocation, regardless of compliance. Data will be entered according to a multiple imputation method. Between-group differences in primary outcomes subsequent to intervention will be compared using multiple linear regression analysis. Baseline scores, experimental groups, and characteristics (e.g., age, sex, diagnoses, and medical conditions) will be included in the models as covariates. If the effects of the intervention are significant, two planned simple contrasts will be performed to assess differences between the EI and control groups and the HI and control groups. Contrasts will also be performed within each intervention group to determine whether intervention benefits are observed for the primary outcomes. The analysis performed for the primary outcomes will also be performed for the secondary and other outcome measures.

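### The primary set is inconsistent and too wide for one alpha of .05: two to five scores, two post-intervention visits, and no control of error across them

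*Protocol article*

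**What the plan says.** - **Primary outcomes section:** "Primary outcomes will include a reduction in depressive symptoms, based on changes in GDS-15 scores, and an improvement in memory performance". Memory is to be assessed by word list memory and by WMS-R Logical Memory. The word list yields two scores (Task I, immediate recognition; Task II, delayed recall). For Logical Memory, "Total scores are calculated (i.e., sum of scores for stories A and B) for WMS-R Logical Memory Tasks I and II". With GDS-15 that makes up to five scores.
- **Abstract:** the primary outcomes are GDS-15 and Logical Memory. Word list memory is not listed.
- **Outcomes section:** all outcomes are collected twice after baseline, at the end of the intervention (6 months) and again 6 months later.
- **Statistical analyses:** groups are compared on the primary outcomes after the intervention by multiple linear regression, with no visit specified. "If the effects of the intervention are significant, two planned simple contrasts will be performed", namely exercise against control and horticulture against control.
- **Sample size:** "The required sample size for this study was calculated using predictions of 6-month changes in GDS-15 results", with "an α level of <.05 to assess the effects of the interventions".

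The article does not rank the primary scores, divide alpha among them, or say whether one or all must be positive.

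**The concern.** A single alpha of .05 has meaning only once the set of tests that can declare success is fixed. Here the two lists of primary outcomes disagree, the longer one is open-ended, and the visit is not settled. A team following the text could regress each of several primary scores on group and present whichever overall test came out significant as a primary result.

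The overall test placed before the contrasts deals with having two active arms. It does not deal with having several scores or two visits. The Discussion expects the findings to go straight into community use, so one favourable memory score among four could carry that message at an error rate well above the one stated. If instead every score had to be positive, error would be contained, but the sample size addresses only GDS-15.

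**Working it through.** **Inputs from the article:** three arms, 1:1:1, 30 per arm; alpha .05 (sidedness not stated, two-sided assumed); overall test, then two contrasts against control; up to five primary scores; two post-intervention visits.

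**Inputs assumed:** all null hypotheses true; each score and visit tested at .05; success if any one score is positive; correlations as shown below.

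**Step 1: the plan's own level, one score at one visit.** The overall F test (2 and 87 degrees of freedom) rejects in 5 % of null trials. With the gate applied, at least one false contrast against control follows in about 4.2 %. This is below 5 % because some overall rejections come with neither control contrast significant. For one score at one visit, the stated .05 is met.

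**Step 2: several independent scores.** The chance of any false overall test is 1 − 0.95^k. The chance of any false gated contrast is about 1 − (1 − 0.042)^k.

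| Tests k | Any overall test | Any gated contrast |
|---|---|---|
| 2 | 9.8 % | 8.2 % |
| 3 | 14.3 % | 12.1 % |
| 5 | 22.6 % | 19.3 % |
| 10 | 40.1 % | 34.9 % |

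**Step 3: correlated scores.** The gated rule was simulated at 30 per arm. The block pattern assumes Logical Memory I with II 0.8, word list I with II 0.5, Logical Memory with word list 0.4, and GDS-15 with memory 0.1.

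| Primary set | Correlation assumed | Any false claim against control |
|---|---|---|
| One depression, one memory score, one visit | 0.1 | about 8 % |
| Abstract's three scores, one visit | independent or block | 10–12 % |
| Five scores, one visit | independent, 0.5 throughout, or block | 16–19 % |
| Five scores, both visits | block, 0.6 between visits | 27–28 % |

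Over a wider set of correlations, five scores give about 13–19 % at one visit and 21–33 % at two. The within-group contrasts that the article also plans on the primary outcomes are not counted.

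**Step 4: if all scores must be positive.** Error cannot then exceed .05. However, Sample size considers only one score ("we predict that a change of 1.5 GDS-15 points would indicate differences", SD 2.5), so no power is justified for joint success.

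**Step 5: price of a stricter first step for GDS-15.** Assume both active arms improve by 1.5 points against control. The arm means are then 0, 1.5 and 1.5, deviating from their average by −1, 0.5 and 0.5. The noncentrality is 30 × (1 + 0.25 + 0.25) / 2.5² = 30 × 1.5 / 6.25 = 7.2. With 2 and 87 degrees of freedom and no baseline adjustment, power of the overall test is 65 % at .05 and 54 % at .025.

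**The case against.** A reader might infer that the trial's true alpha is 16–27 %, that each of five scores is tested at .05 at both visits, and that there is no error control at all. The article does not support this.

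- The .05 appears only in Sample size. No per-score level is given, and no sentence says that one positive score makes the trial positive.
- Neither visit is named as primary. Since sizing uses 6-month change, a single 6-month analysis is a natural reading, and ten primary tests is only one possible count.
- The gate in Statistical analyses is genuine error control between the two contrasts within a score.
- Any inflation figure needs correlations that the article does not contain.

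These points stand, so the percentages describe one possible success rule and are not a property of the plan.

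It can also be said that a multiplicity procedure may sit in a statistical analysis plan that is not shown. That is fair for the procedure itself. It does not cover what the article does state: two different primary lists, one alpha, a testing rule that works within one score, and sizing on one score. An analysis plan could not allocate alpha until the primary scores and visit were settled.

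**Conclusion.** The point holds in a limited form. The Abstract and the Primary outcomes section give different primary sets, the larger with up to five scores. No primary visit is fixed, and the one control in place stops at the boundary of a single score and visit.

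If any one positive score counts as success, the chance of a false claim against control exceeds .05 for every set of two or more scores tried: about 8 % for two, 10–12 % for the Abstract's three, 16–19 % for five at one visit, and about 27–28 % for five at both visits. This rests on two-sided .05 tests per score, all nulls true, 30 analysed per arm and the assumed correlations. If all scores must succeed, error stays within .05 but the trial is not sized for that aim. Either way, the single alpha and the sample size do not match the primary set as written.

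**What to change.** 1. Reconcile the Abstract and the Primary outcomes section so that one closed list of primary scores remains.
2. Name the 6-month visit at the end of the intervention as primary and make the later visit secondary.
3. Keep two primaries: GDS-15 and one memory score, for example one Logical Memory score, since both lists include that test. Move the other memory scores to secondary.
4. Apply Holm to the two overall tests: the smaller p-value against .025, then the other against .05 if the first passes. Run the planned contrasts inside each score only after its overall test passes, at the level that test had to meet. Holm here holds .05 for claims at score level. If each arm-by-score claim must also be held strictly when only one arm works, keep .025 for each score throughout.
5. State the success rule in one sentence.

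An alternative is a fixed sequence with GDS-15, the sizing outcome, first at .05. It costs GDS-15 nothing, but memory is confirmatory only if GDS-15 succeeds. With power for the GDS-15 overall test near 65 % under Step 5, memory would often go untested, so this is a choice for the sponsor.

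**Cost:** a protocol amendment and registry update during enrolment (29 participants recruited at submission), fewer scores that can be claimed as primary, and a stricter first Holm step. Under Step 5 the last takes GDS-15 from 65 % to 54 % power in the worst case, where memory does not pass first. No new data are needed.
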